## Discussion

This study aims to demonstrate that EA is noninferior to solifenacin in reducing UUI episodes in women with urgency-predominant MUI after 12-week treatment.

At present, the diagnostic criteria for urgency-predominant MUI have not been clearly defined. In this study, women will be diagnosed with MUI through history taking, physical examination, questionnaires, voiding diary, specialist diagnosis, and laboratory tests as recommended by the 2018 EAU guidelines. The MESA questionnaire and 3-day voiding diary will be applied to doubly ensure urgency-predominance, which needs to be studied further.

Voiding diaries of 3 and 7 days are reliable in monitoring changes in voiding and incontinence and are thus used as the main tools for outcome assessment. Since urgency is a bothersome symptom in urgency-predominant MUI, overactive bladder, PPIUS, and OAB-q SF are applied to evaluate the severity and the influence on QoL. In this study, both subjective and objective measurements will be applied to assess the outcomes.

In two-arm non-inferiority trials, the choice of a non-inferiority margin is usually based on differences between the active comparator and placebo from previous trials and meta-analyses [22]. However, this approach is problematic for this study because the active comparator in the trial will not necessarily have the same efficacy as previous results in the literature.

A two-arm non-inferiority trial in which a placebo arm is not included is not appropriate due to the lack of assay sensitivity.

The non-inferiority design with a three-arm trial allows indexing of the therapeutic effect of EA based on the performance of Solifenacin and SA within the trial, instead of using external references, as further discussed. Therefore, it is considered the “gold standard” of non-inferiority trials according to the US Food and Drug Administration (FDA) and the European Medical Agency (EMA) [23].

However, the placebo of Solifenacin is rather difficult to access in China, making the blinding of all patients impossible in a three-armed non-inferiority trial. Therefore, the efficacy of solifenacin (solifenacin plus SA) compared with a placebo (Placebo plus SA) cannot be assessed.

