## Methods and analysis

### Study design

The study will be a multicentered, randomized, three-armed, non-inferiority clinical trial with sham electroacupuncture (SA) and solifenacin as controls. The null hypothesis is that the improvement (difference in the number of UUI episodes between baseline and 12-week assessment) in the EA group would be 50% or less of the difference in improvement between the solifenacin and SA groups; that is, noninferiority would be established if EA, compared with solifenacin, retains at least 50% of the efficacy of solifenacin over SA. The outcome assessors and statisticians will be blinded. Patients in the EA and SA groups will be blinded, while those in the solifenacin group will not be blinded. The study will be carried out after the ethics is approved by the Institutional Review Board. All the patients in the study will be informed about the details of the study and written informed consent will be obtained before enrollment.

In the written informed consent, the participants will be informed that if they are eligible and willing to participate in the study, they will be randomized into the EA group, SA group, or solifenacin group with the same probability. The investigators plan to enroll 282 participants, with 94 in each group. Solifenacin is an effective treatment for the UUI component, as recommended by the current guidelines, and our previous studies indicated that EA and SA are both effective for urgency-predominant MUI to some degree. In the EA group, participants will receive traditional EA at traditional acupoints, while participants in the SA group will receive shallow and minimal EA at non-acupoints.

The study is designed and reported in accordance with the Consolidated Standards of Reporting Trials (CONSORT) guidelines, the Standard Protocol Items: Recommendations for Interventional Trials (SPIRIT) Checklist, and Standards for Reporting Interventions in Controlled Trials of Acupuncture (STRICTA) recommendations. The protocol has been reviewed, revised, and supported by experts in statistics, urology, and acupuncture.

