### Subjects

#### Sample size calculation

The sample size was calculated based on our previous study [10]. The expected drop-out rate is 10% and the noninferiority margin is 50% of the comparative efficacy between SA and Solifenacin. The noninferiority margin was set based on our hypothesis that EA will be associated with at least 50% of the difference in the efficacy of solifenacin as compared with that of SA.

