### Statistical analysis

For the primary hypothesis, we will compare the decrease in UUI episodes among the three groups. A decrease in number will indicate less incontinence. Additionally, we will use a modified *t*-test based on the retention of effect method to analyze whether EA is noninferior to solifenacin [21]. In detail, to establish the assay sensitivity of the trial, a *t*-test investigating the superiority of solifenacin over SA will be performed first by comparing the decrease in the number of UUI episodes in the solifenacin and SA groups. After superiority has been established, a modified *t*-test will be used to assess whether the difference in the numbers between the EA and SA groups is more than 50% of the mean difference between the numbers in the solifenacin and SA groups. An appropriate Fieller’s confidence interval can also be provided [21]. If the *P* Value is equal to or less than 0.025 or if the lower boundary of the confidence interval around the mean difference between the numbers in the EA group versus that in the solifenacin group exceeds this value, then noninferiority will be established. After the noninferiority assessment, traditional *t*-tests will be used for superiority analyses, including a decrease in the number of UUI episodes for solifenacin versus EA, and EA versus SA.

A mixed-effect model or Wilcoxon rank-sum test will be used to assess the longitudinal continuous variables. A generalized linear model or logistic regression will be performed to assess the rates of response. Chi-square or Fisher’s exact tests will be used to compare the frequency of AEs between groups.

Primary outcome analysis will be performed in the intention-to-treat (ITT, randomized participants) and per-protocol datasets (PP, ITT participants who received at least one treatment session without major violation of the protocol). Missing data will be imputed using the multiple imputation method under the missing-at random assumption. Secondary and safety outcomes will be assessed in ITT populations.

Since all analyses other than the primary analysis are considered descriptive, no adjustments will be made for multiple testing, and *P* values should be interpreted accordingly. Analyses will be performed using SAS version 9.4 (SAS Institute Inc) with a two-sided *P* value of less than .05 considered significant.

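### Open-label solifenacin beating sham acupuncture does not establish assay sensitivity, so the non-inferiority conclusion must stay relative to the sham arm

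*Protocol article*

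**What the plan says.** - **Criterion.** Under Study design, "noninferiority would be established if EA, compared with solifenacin, retains at least 50% of the efficacy of solifenacin over SA". Under Sample size calculation, "the noninferiority margin is 50% of the comparative efficacy between SA and Solifenacin". Both are worded relative to SA.
- **Testing order.** Under Statistical analysis, a t-test "investigating the superiority of solifenacin over SA will be performed first", and its stated purpose is "to establish the assay sensitivity of the trial". If it succeeds, a modified t-test asks "whether the difference in the numbers between the EA and SA groups is more than 50% of the mean difference" between solifenacin and SA. Passing that test is said to establish non-inferiority, with no mention of SA in the conclusion.
- **Status of SA.** Study design states that "our previous studies indicated that EA and SA are both effective for urgency-predominant MUI to some degree".
- **Blinding.** Study design and Blinding say that EA and SA patients are blinded and solifenacin patients are not. Table 2 gives EA and SA patients 36 needling sessions. The solifenacin section describes tablets only.
- **Justification.** The Discussion rejects two-arm non-inferiority trials that have no placebo arm, because they lack assay sensitivity. It says the three-arm design "allows indexing of the therapeutic effect of EA based on the performance of Solifenacin and SA within the trial" and that regulators regard such designs as the gold standard. It then concedes that, with no solifenacin placebo available, "the efficacy of solifenacin (solifenacin plus SA) compared with a placebo (Placebo plus SA) cannot be assessed".

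**The concern.** A three-arm retention design provides assay sensitivity when the third arm is a placebo for both active treatments. The contrast of active control with placebo then isolates the control's effect, and that effect is the yardstick for the new treatment. Here SA plays that part for EA but not for solifenacin. The Discussion's own parentheses show what a proper contrast would need: drug plus SA against placebo plus SA. Neither arm exists in this trial.

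The reading of the result is at stake in two places. A pass would be reported as non-inferiority to solifenacin, when the trial shows only that EA's advantage over SA is at least half of open-label solifenacin's advantage over SA. A failed step 1 could be taken as a sign that the trial cannot detect effective treatments, or that the drug does not work, when SA may simply have done well.

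**Working it through.** **The plan's own figures.** 3 × 94 = 282 and 42 + 5 × 48 = 282, so the total agrees with the arms and the sites. Also 84/(1 − 0.10) = 93.3, which rounds up to 94, so 84 evaluable per arm is used below. The article gives no effect size, SD or power, so 282 can be neither confirmed nor refuted.

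**Model (an assumption).** Mean improvement by arm:
- solifenacin: p + d
- SA: a
- EA: a + e

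Here d and e are the specific effects of drug and EA, p is the non-specific effect of the open pill, and a is that of sham needling. The documents give none of these.

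**Step 1 tests d + p − a, not d.** Its standard error is SD × √(2/84) = 0.154 SD. If the drug is inert (d = 0) and p − a = 0.5 SD, power is Φ(0.5/0.154 − 1.96) = 90%. At p − a = 0.3 SD it is 49%. A test that an inert drug can pass this often does not prove assay sensitivity. In the other direction, with d = 0.75 SD and a − p = 0.5d, the contrast is 0.375 SD and step 1 succeeds only 68% of the time although the drug works.

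**Retention boundary, specific effects.** The boundary is e = 0.5(d + p − a), so e/d = 0.5 × [1 − (a − p)/d].

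| (a − p)/d | e/d at the 50% boundary |
|---|---|
| −0.25 | 62.5% |
| 0 | 50% |
| 0.25 | 37.5% |
| 0.50 | 25% |
| 0.75 | 12.5% |

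Take d = 0.75 SD and a true e/d of exactly 50%. The simulated chance of passing both steps is 0.4% at (a − p)/d = −0.25, 2.5% at 0, 10.0% at 0.25 and 19.8% at 0.50.

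**Retention boundary, total effects.** Now measure every arm against one common no-effect reference, and let SA have share s of solifenacin's total effect. At the boundary EA's share is s + 0.5(1 − s) = 0.5 + 0.5s: 50% at s = 0, 62.5% at s = 0.25 and 75% at s = 0.50. On this scale an active SA makes the criterion stricter.

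**The two results agree.** With p = 0 and s = 0.50, EA's specific part is 25% of solifenacin's effect and its total is 25% + 50% = 75%. The same trial result looks lenient or strict depending on which quantity is meant by efficacy.

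**Power.** The retention contrast EA − 0.5 × solifenacin − 0.5 × SA has variance 1.5 SD²/n. If EA equals solifenacin, n = 84 and one-sided alpha is 0.025, then 80% power (assumed) needs a solifenacin-SA gap of √(6 × (1.96 + 0.842)²/84) = 0.75 SD. If SA's activity narrows the gap to 0.5 SD, power is Φ(0.25/√(1.5/84) − 1.96) = 46%. At 0.4 SD it is 32%.

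**The case against.** - **The criterion is always relative to SA.** This stands. Study design, Sample size calculation and the modified t-test all say so, and the design can estimate and test that quantity. A reader might infer that the retention claim is undeliverable. The documents do not support that. What the design cannot deliver is retention of solifenacin's placebo-controlled effect, and the SA qualifier is missing where Statistical analysis draws its conclusion and where the Discussion states its aim.
- **An effective sham might be thought to make the test too easy.** The documents do not support this either. On total effects an active SA makes the test stricter. Leniency requires the drug's specific effect as the yardstick and sham needling with a larger non-specific effect than open tablets, and no passage says that it has.
- **SA as an active treatment.** Study design calls SA effective to some degree but does not say against what. Improvement from baseline would fit the sentence.
- **The limitation is disclosed.** This stands. The abstract and Discussion state it, and the gold-standard sentence is later qualified for this trial. The disclosure is not carried back to Statistical analysis, where the assay-sensitivity label and the unqualified conclusion remain.
- **Step 1 is only a gate.** This also stands. No passage says that failure would be read as evidence against solifenacin. Because it could be read so, one sentence should rule it out.
- **The component comparisons are already planned.** This is true of EA against SA and of solifenacin against EA, so only their presentation beside the retention result is at issue.

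**Conclusion.** The point holds as an inconsistency between what Statistical analysis claims and what the Discussion concedes. Open-label solifenacin against SA neither proves assay sensitivity nor isolates solifenacin's efficacy, so an unqualified conclusion of non-inferiority to solifenacin goes further than the design allows. This rests on the documents' own statements and needs no outside figure.

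The size and direction of any distortion in the 50% criterion are unknown. The percentages in the working depend on assumed values of a − p, on d = 0.75 SD or the other stated gaps, and on 84 evaluable per arm. They show that the effect could be material in either direction, not that a bias of a given size exists. No sample-size error is shown.

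**What to change.** 1. In Statistical analysis, rename step 1 *superiority of open-label solifenacin over SA* and drop the assay-sensitivity claim.
2. In Statistical analysis and Discussion, carry through the qualifier from Study design, so that the conclusion reads: *EA's advantage over SA is at least 50% of open-label solifenacin's advantage over SA*.
3. In the Discussion, state that the gold-standard argument does not fully apply because SA is not a placebo for solifenacin.
4. Add that failure of step 1 does not show that solifenacin is ineffective.
5. Show the already planned EA-SA and EA-solifenacin differences, with confidence intervals, beside the retention result.

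The cost is a few sentences and a less favourable headline claim. Recruitment has started, but no arm, test or sample size changes.

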## Trial status

The recruitment has already started.

## Data Availability

The datasets used and/or analyzed during the current study are available from the corresponding author on reasonable request anonymously.

## Abbreviations

ICIQ SF: International Consultation on Incontinence Questionnaire Short Form
MUI: Mixed urinary incontinence
OAB-q SF: Overactive bladder questionnaire short form
PGI-I: Patient global impression improvement
PGSC: Patient Global Symptom Control
PPIUS: Patient Perception of Intensity of Urgency Scale
SUI: Stress urinary incontinence
UI: Urinary incontinence
UUI: Urgency urinary incontinence
